#### 4.1 General Design

This is an open label, single-center phase I study of TRACT in living donor renal transplant recipients. This safety portion of this study will continue for six months but the patients will be followed for up to 60 weeks. Participants will receive “standard of care” immune suppression, living donor kidney transplantation and TRACT. Prior to the kidney transplant, blood will be collected for immunophenotypic analysis of circulating leukocytes by flow cytometry, as well as functional immune assays. **Dose escalation of nTregs will be based upon the absence of infusion related side effects and specific adverse events (subsequent rejection episodes, allosensitization, development of opportunistic infection) within 30 days of infusion.**

Patients will undergo living donor kidney transplantation using immunosuppression based upon the standard of care regimen using alemtuzumab and the avoidance of oral corticosteroids (46, 47). This immunosuppressive regimen has been used for more than a decade at Northwestern in more than 2000 kidney transplant recipients. All patients will receive two doses of alemtuzumab (Campath-1H, 30mg); one at the time of renal transplant, and one on post-operative day two to achieve peripheral T-cell depletion. Intravenous glucocorticoids will be administered prior to Campath administration to limit cytokine release syndrome in association with this monoclonal antibody, and continued for the first two days post-transplant. Thereafter, steroids will not be used for immunosuppression. All transplant recipients will be started on oral immunosuppressive therapy with MPA and tacrolimus prior to transplant. After 30 days, patients will be converted to the combination of Sirolimus and MPA, as the inhibition of IL2 production by CNIs would impair the survival of infused expanded Tregs.

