## SCHEDULE OF EVENTS: SAMPLE COLLECTION FOR TRACT STUDY

[figure not shown]

Escalating doses of autologous expanded Tregs (TRACT) will be administered to the next cohort of patients if there are no observed serious adverse events within 30 days of TRACT infusion as follows:

Tier 1:  $0.5 \times 10^9$  total expanded Tregs (n=3)

Tier 2:  $1 \times 10^9$  total expanded Tregs (n=3)

Tier 3:  $5 \times 10^9$  total expanded Tregs (n=3)

Tier 4:  $8 \times 10^9$  total expanded Tregs (n=3)

Patients will be monitored at various time points, as described above for evidence of donor-specific transplantation tolerance using in vitro analyses, specifically mixed-leucocyte reaction assays (MLR). Graft function will be monitored clinically in the standard fashion. The overall goal for this phase I study is to demonstrate the safety of TRACT administration in kidney transplant recipients, and lay the foundation for a subsequent phase 2 trial. If we are successful, this approach could have for a transformative effect upon the field of solid organ and cellular transplantation.

The clinical site for recruitment, enrollment, and treatment of patients will be Northwestern Memorial Hospital. The Principal Investigator is part of a team with the most active living donor renal transplant program in the nation, with more than 160 such transplants performed in 2011. There already exists a robust infrastructure for combined therapeutic cell transfer (stem cell) and solid organ transplantation with two protocols for living donor renal transplants + HSC having been active at Northwestern for almost 5 years; [name], the IND sponsor and co-investigator, serves as PI or co-PI on these trials (50, 51).

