## 4.2 Primary Safety Endpoint

The primary safety endpoint is the evaluation of cellular related toxicities immediately and within 24 hours post-infusion of TRACT. Since TRACT is being administered to promote immunosuppression and prevent rejection, specific adverse events (subsequent rejection episodes, allosensitization, development of opportunistic infection) within 30 days of infusion will be monitored.

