A dose-limiting toxicity (DLT) is defined as a clinically significant adverse event or abnormal laboratory value assessed as unrelated to the kidney transplant, intercurrent illness, or concomitant medications and occurring during the first 3 weeks after administration of the first dose that meets any of the following criteria: grade 3 or 4 non-hematologic toxicity (except for electrolyte disturbances responsive to correction measures within 48h, diarrhea, nausea and vomiting that responds to standard medical care, rash  $\geq$  Grade 3 that response to supportive care, infusion relation reaction that are responsive to supportive care, infections and infectious complications related to patients neutropenia, elevated creatinine  $<3.5 \times$  upper limit of normal, elevated AST  $< 8 \times$  upper limit of normal, elevated ALT  $<8 \times$  upper limit of normal, elevated bilirubin  $< 5 \times$  upper limit of normal, elevated PTT  $< 3.5 \times$  upper limit of normal).

Dose escalation will only occur after patients, at a given dose level, have been followed for at least 21 days and no evidence of dose limiting toxicity has been seen. The dose level for a given patient and the progression of doses from one cohort of patients to the next will be adjusted based on adverse events. If a patient is discontinued due to concurrent illness unrelated to toxicity or organ rejection before they reach the end of the treatment cycle (21 days after the infusion), an additional patient will be enrolled at that same dose level.

| No. of Patients with DLT at a Given Dose Level | Escalation Decision Rule                                                                                                                                                                                                                                              |
|------------------------------------------------|-----------------------------------------------------------------------------------------------------------------------------------------------------------------------------------------------------------------------------------------------------------------------|
| 0 out of 3                                     | Enter patient(s) at the next dose level.                                                                                                                                                                                                                              |

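### Section 4.1 and section 7.4 give incompatible dose-escalation rules, and the DLT definition keeps rejection and donor sensitization out of the count that drives the table

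*Protocol*

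**What the plan says.** The protocol describes the escalation condition in four places.

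- **Treatment Schema (Study Summary):** the cell dose goes up if there are no adverse events in the 30 days after infusion, with no restriction on type or grade.
- **Section 4.1:** "Dose escalation of nTregs will be based upon the absence of infusion related side effects and specific adverse events". The specific events are rejection, allosensitization and opportunistic infection, again over 30 days.
- **Text under the Schedule of Events:** the next cohort is dosed "if there are no observed serious adverse events within 30 days of TRACT infusion".
- **Section 7.4:** a 3+3 table driven by DLT counts. With no DLT among three patients, the next patients enter the higher level. A DLT must be "assessed as unrelated to the kidney transplant, intercurrent illness, or concomitant medications", must be "occurring during the first 3 weeks after administration of the first dose", and must be a "grade 3 or 4 non-hematologic toxicity", subject to a list of exceptions that includes "infections and infectious complications related to patients neutropenia".

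Section 4.2 defines the primary safety endpoint as cell-related toxicity up to 24 hours after infusion, and adds that "specific adverse events (subsequent rejection episodes, allosensitization, development of opportunistic infection) within 30 days of infusion will be monitored". Section 3.1 places rejection, allosensitization and nonspecific immunosuppression within the primary objective.

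Section 7.5 sets study-level rules. Two of five patients with grade 3-4 infusion reactions, or with grade 4 organ toxicity within 30 days, halt the study, as does a death from those causes. Two of three consecutive subjects with severe steroid-resistant or vascular rejection, graft loss, malignancy, severe infection or death within three months stop enrollment.

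**The concern.** An escalation rule has to return one answer for one set of data. Here the section that describes the design and the section that operates it look at different events over different windows. The attribution clause in the DLT definition also removes some of the events on which section 4.1 says escalation turns.

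Section 1.9 presents the trial as the first use of recipient-derived Tregs in adult kidney transplantation, and the dose rises sixteenfold across four tiers (0.5 to 8 × 10⁹ cells). The decision to go up is the main decision the trial makes. If the team follows the table, it can escalate past events that section 3.1 sets out to study. If it follows section 4.1, a single rejection holds a tier that the table would pass.

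**Working it through.** **Design figure.** Four tiers of three patients give 4 × 3 = 12, which matches the stated enrollment. Nothing below disputes that number.

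**Events set against the two rules.**

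| Event after infusion | Section 4.1 | DLT count in section 7.4 |
|---|---|---|
| Rejection | Blocks escalation | Not counted: cannot be unrelated to the transplant |
| Sensitization to the donor | Blocks escalation | Not counted: the infused cells are the recipient's own (section 2.2), so the donor antigen comes from the graft |
| Opportunistic infection with neutropenia | Blocks escalation | Exempted by name |
| Other opportunistic infection, grade 3-4 | Blocks escalation | Depends on attribution: drops out if assigned to immunosuppression or intercurrent illness |
| Any of these on days 22-30 | Blocks escalation | Outside the window |

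**Windows.** 30 − 21 = 9 days, or 9/30 = 30% of the section 4.1 window, lie outside the DLT window. With infusion on day 60, the DLT window closes at day 60 + 21 = 81 and the 30-day window at day 60 + 30 = 90. The protocol biopsy and immune monitoring in section 7.3 are due at month 3, about day 90. A rejection first seen on that biopsy is too late for the DLT count and falls at about the close of the 30-day window.

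**A case that splits the rules.** Take a tier in which all three patients have mild, steroid-responsive, non-vascular rejection within 30 days.

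1. Section 4.1: the condition is not met, so there is no escalation.
2. Section 7.4 table: zero DLTs in three, so the next patients enter the higher dose.
3. Section 7.5, two-of-three rule: not triggered, because the rejection is neither severe and steroid-resistant nor vascular, and no graft is lost.
4. Sections 7.4 and 9.4: the investigators, the IND sponsor and the medical monitor review before escalation, but no rejection or infection criterion is given to them.

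The replacement sentence in section 7.4, on patients discontinued before day 21, does not settle the matter. It can be read as keeping a patient discontinued for rejection in the cohort or as replacing that patient. Neither reading counts the rejection.

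**Illustration of size.** Let p be the per-patient 30-day risk of an event that section 4.1 counts and the DLT definition does not. The protocol gives no such rate. Section 2.3 mentions acute rejection below 10%, without a time window, so p is an assumption shown over a range. Assume independent patients and no DLT in the tier. The table then passes the tier, while section 4.1 passes it with probability (1 − p)³.

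| p (assumed) | Section 4.1 passes: (1 − p)³ | The rules disagree: 1 − (1 − p)³ |
|---|---|---|
| 0.10 | 0.9³ = 0.729 | 0.271 |
| 0.30 | 0.7³ = 0.343 | 0.657 |
| 0.50 | 0.5³ = 0.125 | 0.875 |

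**Grade limit.** The DLT criterion names grades 3 and 4 only. Read literally, a fatal toxicity adds nothing to the DLT tally or to the limit of one in six that defines the maximum tolerated dose.

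**The case against.** The strongest reply is that the table is not the only gate. The 30-day conditions in section 4.1 and under the Schedule of Events remain in force. Many rejections and opportunistic infections would be serious adverse events under section 9.1. Section 7.4 itself says dose progression is adjusted for adverse events generally, and review precedes each escalation. That stands against a reading a reader might be tempted to make, that the protocol would escalate with certainty whatever the rate of these events. The table cannot block escalation on rejection or donor sensitization, but other text and the reviewers could. What the reply does not remove is that the gates conflict and nothing says which prevails.

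Three other stronger readings also fail.

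- **That the DLT definition excludes all opportunistic infection.** Only neutropenia-related infection is exempted by name. A non-neutropenic grade 3-4 infection judged unrelated to drugs and illness would count. Section 1.1 says immunosuppressants predispose to infection, but that does not decide individual attribution.
- **That these events are the primary safety endpoint.** Section 4.2 lists them as monitored; the endpoint it states is toxicity up to 24 hours. The main conflict is between sections 4.1 and 7.4.
- **That a fatal toxicity goes unanswered.** Section 7.5 halts the study for a death from its listed toxicities, a stronger response than scoring one DLT. The gap concerns the tally, not protection as such.

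**Conclusion.** The point holds as a contradiction between stated decision rules on a safety matter, and it should be resolved before the rules are relied on. Sections 4.1 and 7.4 can give opposite escalation decisions on the same data. For rejection and donor sensitization the mismatch is built into the attribution clause; for opportunistic infection it is certain only when the infection is neutropenia-related, and otherwise turns on judgement. The windows differ by nine days.

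This conclusion rests on the text alone. The probabilities (section 4.1 passing a tier 73%, 34% and 12.5% of the time at assumed risks of 10%, 30% and 50%) only show that the disagreement would not be rare if such events are at all common. They assume independent patients and no DLTs, and they describe the written rules before any discretionary review. The missing grade 5 is a secondary wording gap.

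**What to change.** Reconcile the Treatment Schema, section 4.1, the text under the Schedule of Events, section 4.2, section 7.4 and section 7.5 so that one set of events and one observation window governs escalation. The reconciled text should state:

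- whether rejection, allosensitization and opportunistic infection govern escalation, with the attribution clause in section 7.4 and the condition in section 4.1 made to agree with that answer;
- how a fatal event counts in the DLT and maximum-tolerated-dose tally, consistently with the halt in section 7.5.

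Which events, grades and window to use is a clinical choice for the sponsor.

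The cost is a short text edit across these sections. The downside is that, if the events are counted, background rejection or infection unrelated to the cells may delay or expand a tier, and the 12-patient total could be exceeded. If they are not counted, section 4.1 can no longer present them as escalation criteria.

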## 5 Subject Selection

The target population is adult recipients of immediately functioning living donor renal allografts. Immediate function will be defined as the absence of the need for hemodialysis in the first week following renal transplantation.

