### 5.2 Exclusion Criteria

1. Known sensitivity or contraindication to Sirolimus, tacrolimus or MMF.
2. Patient with significant or active infection.
3. Patients with a positive flow cytometric crossmatch using donor lymphocytes and recipient serum.
4. Patients with PRA >20%.
5. Patients with current or historic donor specific antibodies.
6. Body Mass Index (BMI) of < 18 or > 35.
7. Patients who are pregnant or nursing mothers.
8. Patients whose life expectancy is severely limited by diseases other than renal disease.
9. Ongoing active substance abuse, drug or alcohol.
10. Major ongoing psychiatric illness or recent history of noncompliance.
11. Significant cardiovascular disease (e.g.):
  - Significant non-correctable coronary artery disease;
  - Ejection fraction below 30%;
  - History of recent myocardial infarction.
12. Malignancy within 3 years, excluding nonmelanoma skin cancers.
13. Serologic evidence of infection with HIV or HBVsAg positive.
14. Patients with a screening/baseline total white blood cell count  $\leq 4,000/\text{mm}^3$ ; platelet count  $\leq 100,000/\text{mm}^3$ ; triglyceride  $\geq 400$  mg/dl; total cholesterol  $\geq 300$  mg/dl.
15. Investigational drug within 30 days prior to transplant surgery.

14. Anti-T cell therapy within 30 days prior to transplant surgery.

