## **7.4 Dose Limiting Toxicity (DLT) Determination in the Study**

This is an open-label, single arm, dose escalation- de-escalation, phase I safety study which will examine the feasibility and safety of infusing autologous regulatory T cells (Tregs) into patients who have received a living donor kidney transplant. Tregs will be administered approximately 60 days post kidney transplantation.

According to the phase I dose escalation/de-escalation study design described below. The 4 dose levels are:  $0.5 \times 10^9$ ,  $1 \times 10^9$ ,  $5 \times 10^9$ ,  $8 \times 10^9$  Treg cells. All patients will be observed for a minimum of four hours following infusion and cell related toxicities monitored for the next three weeks. Patients with grade 3 or 4 toxicity during the infusion will have their cellular administration discontinued immediately and the event noted as a dose-limiting toxicity.

Adverse event information from the infusion will be used to determine whether the next subject within each cohort will receive the dose of cells associated with that dose level. The PI, IND Sponsor, IND Medical Monitor and study co-investigators will review toxicity reports and recommend whether or not it is safe to proceed at this dose level for the next patient. The next patient within a dose level will only be administered Treg after the first patient has been followed for at least 21 days and no evidence of dose limiting toxicity has been seen. The dose level for a given patient and the progression of doses from one cohort of patients to the next will be adjusted based on adverse events.

Adverse event information from the infusion will be used to determine whether or not dose escalation or de-escalation to the next level will occur. Adverse events will be graded using the Common Toxicity Criteria for Adverse Events, version 4.0e (NCI-CTCAE v4).

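### After infusion, section 7.4 counts an attributed cytopenia, or a creatinine rise below 3.5 times the upper limit of normal, as no DLT for escalation or MTD, in conflict with the protocol's 30-day escalation rules

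*Protocol*

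**What the plan says.** Section 7.4 defines a DLT as a clinically significant event that is "assessed as unrelated to the kidney transplant, intercurrent illness, or concomitant medications" and is "occurring during the first 3 weeks after administration of the first dose". The event must also meet any of the criteria that follow. One criterion follows: "grade 3 or 4 non-hematologic toxicity (except for electrolyte disturbances responsive to correction measures within 48h". The list of exceptions continues and includes "infections and infectious complications related to patients neutropenia, elevated creatinine", the creatinine exception applying below 3.5 times ULN.

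The table in 7.4 acts on the DLT count. For 0 of 3 the instruction is "Enter patient(s) at the next dose level". The text after the table defines the MTD as the highest level with at most one DLT among six patients.

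Separate wording in 7.4, repeated in 7.5, covers the infusion itself: "Patients with grade 3 or 4 toxicity during the infusion will have their cellular administration discontinued immediately", and the event is recorded as a DLT.

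Three other places also govern escalation, each over 30 days:
- The Treatment Schema requires that there be no adverse events.
- The bold sentence in 4.1 requires that there be no infusion side effects, rejection, allosensitization or opportunistic infection.
- The tier listing after the Schedule of Events requires that there be no serious adverse events.

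**The concern.** Background cytopenia from alemtuzumab, mycophenolate or sirolimus would be a natural reason to leave hematologic toxicity out. But the same sentence already removes events attributed to concomitant medication. What the omission removes in addition is a cytopenia that the investigators did not put down to those drugs, the transplant or another illness.

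The creatinine exception is tied to the laboratory's ULN and not to the patient's own level. Yet section 5 states that "The target population is adult recipients of immediately functioning living donor renal allografts", and the primary objective in 3.1 includes whether the product leads to rejection.

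At stake are two decisions that run on DLT counts: whether the next tier opens under the table, and which dose is declared the MTD. If the 30-day rules stop escalation on an event that 7.4 scores as zero, the protocol gives two answers for the same cohort.

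**Working it through.** **1. The plan's own figure.** Four tiers of three patients give 4 × 3 = 12, the stated number of subjects. The protocol gives no target DLT rate and no operating characteristic to reproduce.

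**2. The rules side by side, for events after the infusion that pass attribution.**

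| Event | 7.4 table and MTD | Treatment Schema | 4.1, bold sentence | 4.1, tier listing |
|---|---|---|---|---|
| Grade 3–4 cytopenia, laboratory finding only | 0 DLT | blocks if recorded as an adverse event | not named | blocks only if serious |
| Neutropenia-related infection | 0 DLT | blocks | blocks if opportunistic | blocks if serious |
| Creatinine rise, below 3.5 × ULN | 0 DLT | blocks if recorded as an adverse event | blocks if it reflects rejection | blocks if serious |

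The rules also differ in time. Infusion is at day 60. The DLT period ends at day 60 + 21 = 81, and the 30-day rules end at day 60 + 30 = 90. The table also allows escalation after one DLT in six patients, which the Treatment Schema does not.

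**3. The table alone.** Let p be the chance per patient of the event. If it counts, the table escalates after 0 of 3, or after 1 of 3 followed by 0 of 3:

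P(escalate) = (1 − p)³ + 3p(1 − p)² × (1 − p)³

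- p = 0.30: 0.343 + 0.441 × 0.343 = 0.494
- p = 0.50: 0.125 + 0.375 × 0.125 = 0.172

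If the event does not count, it leaves the count at 0 of 3 and P(escalate) = 1.00 at any p, as far as this toxicity is concerned. The rates are assumptions; the protocol gives none.

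**4. Effect of attribution.** If only a share f of events passes the attribution test, the rate that counts is p × f. With p = 0.50 and f = 0.6 it is 0.30, and P(escalate) = 0.494. With f = 0.2 it is 0.10, and P(escalate) = 0.729 + 0.243 × 0.729 = 0.906. The values of f are also assumptions.

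**5. Creatinine.** If clearance varies as 1/creatinine at steady state, a rise from b × ULN to just under 3.5 × ULN means a fractional loss of 1 − b/3.5:

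- b = 1.0: 71%
- b = 1.5: 57%
- b = 1.75: 50%
- b = 2.0: 43%

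The protocol gives no value of b.

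**The case against.** A reader might infer that a tier with such events simply clears and the dose rises. The documents do not support that.

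- The three 30-day rules could each stop escalation.
- Section 7.4 says that dose progression is adjusted on adverse events, and it requires a review of toxicity reports before the next cohort.
- Section 7.5 halts the study if 2 of 5 patients have grade 4 organ toxicity within 30 days. It stops enrollment if two of three consecutive subjects have, among other events, severe infection or graft loss within three months.

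Nor does the protocol count only non-hematologic toxicity throughout: any grade 3 or 4 toxicity during the infusion is a DLT. The gap concerns the three weeks that follow.

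A reader might also take the creatinine exception to hide the loss of most graft function. It covers a laboratory value, not rejection or graft loss as such, and a loss above 50% requires a baseline below 1.75 times ULN. Major dysfunction would often surface as rejection or as a serious event. The marrow part is therefore the stronger one.

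Finally, 1.00 against 0.17 is no operating characteristic of this trial. The infusional toxicity table in 1.4 lists no cytopenia, and every patient takes drugs for which section 2.1 lists blood-count effects, so few cytopenias may pass attribution.

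All of this limits the size. It does not remove the defect. The 30-day rules differ from one another and from the 21-day table. The review states no criterion for these events. The 7.5 halt leaves out grade 3 and does not say whether marrow is an organ. None of these rules enters the MTD definition.

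**Conclusion.** The point holds in a limited form. For events after the infusion, 7.4 promises several criteria and gives one. An attributed cytopenia, a neutropenia-related infection or a creatinine rise below 3.5 times ULN then scores zero in the table and in the MTD definition. The Treatment Schema and 4.1 could stop escalation on the same event, so the protocol contradicts itself on when a tier is cleared.

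For the table alone, the difference is 1.00 against 0.49 at an assumed 30% rate and 1.00 against 0.17 at 50%, if every event passes attribution. It shrinks as fewer do. The creatinine range corresponds to a loss of about 43% to 71% of clearance for assumed baselines of 2.0 to 1.0 times ULN. The conflict between the passages depends on none of these assumptions. It should be resolved, because both the next dose and the MTD depend on it.

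**What to change.** Reconcile section 7.4 with the Treatment Schema, both rules in 4.1, and 7.5, so that one rule with one observation period governs both escalation and the MTD. That rule should state:

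- whether hematologic toxicity that passes attribution counts as a DLT;
- whether a neutropenia-related infection that passes attribution counts;
- against which reference creatinine is judged;
- how the infusion-time wording and the 7.5 halt relate to the DLT count.

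Grades, durations and thresholds are for the sponsor to set.

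The main cost is amendment wording. Section 7.3.2 already schedules hematology and chemistry at weeks 8 and 10. Counted from transplant, these are days 56 and 70, on either side of the day-60 infusion. Week 10 is the only scheduled draw inside the 21-day period, since week 12 is day 84, so a criterion based on duration might need another draw. The statistical downside is that a misattributed event could occasionally expand a tier from 3 to 6 patients.

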Once a cohort is filled, enrollment into the next dose level will only begin after all patients in that cohort have passed through the DLT observation period. At that point, the PI, IND Sponsor, IND Medical Monitor and study co-investigators will review toxicity reports and recommend whether or not it is safe to proceed to the next cohort.

After escalation has stopped, de-escalation will begin at one dose level below the maximum achieved during escalation. The action taken depends on the number of patients previously treated at a dose level. If 3 or fewer patients have previously been treated, 3 patients are added; if 6 patients have previously been treated, this level will be declared to be the MTD. The MTD is defined to be the highest dose level at which no more than 1 of 6 treated patients experiences a DLT.

Patients within a cohort need not be accrued or treated at the same time; thus, accrual at a dose level should stop as soon as 2 patients at a dose level have experienced DLT at that level. There will be no intra-patient dose escalation or de-escalation.

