## 7.5 Stopping Rules

The Principal Investigator may terminate the trial after consultation with the appropriate consulting staff at any time.

Patients with grade 3 or 4 toxicity during the infusion will have their cellular administration discontinued immediately and the event noted as a dose limiting toxicity.

The study as a whole will be halted if 2/5 patients develop grade 3-4 infusion reactions, or grade 4 organ toxicity within the first 30 days following Treg infusion. The study will also be halted if a death results from any of the criteria listed above.

If two of three consecutive subjects receiving experience severe steroid resistant acute rejection, vascular acute rejection, graft loss, malignancy, severe infection, and/or death in a period of 3 months, enrollment will be stopped and the study reassessed by the investigators, the IND sponsor and IND medical monitor.

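### A grade 3-4 reaction that begins during the infusion and responds to care is a DLT under one rule in section 7.4 (repeated in 7.5) and not a DLT under the DLT definition in 7.4

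*Protocol*

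**What the plan says.** Three statements in the protocol bear on how the event is scored.

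- **Section 7.4, second paragraph.** Patients with grade 3 or 4 toxicity during the infusion "will have their cellular administration discontinued immediately and the event noted as a dose-limiting toxicity". No exception is given.
- **Section 7.5.** The same rule again: the infusion is "discontinued immediately and the event noted as a dose limiting toxicity".
- **Section 7.4, DLT definition.** A DLT is a grade 3 or 4 non-hematologic toxicity in the first three weeks, subject to a list of exceptions. One of these is "infusion relation reaction that are responsive to supportive care". Vomiting that responds to standard care and rash of grade 3 or higher that responds to supportive care are also excepted.

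The DLT count then feeds three decisions in section 7.4:

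- the escalation table (0 of 3 escalate, 1 of 3 add at least three patients, 2 or more stop);
- the within-tier gate, under which the next patient is dosed only "after the first patient has been followed for at least 21 days and no evidence of dose limiting toxicity has been seen";
- the MTD: "The MTD is defined to be the highest dose level at which no more than 1 of 6 treated patients experiences a DLT".

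Other rules act alongside the count. Section 4.1 states: "Dose escalation of nTregs will be based upon the absence of infusion related side effects". The text under the schedule of events allows the next cohort "if there are no observed serious adverse events within 30 days of TRACT infusion". Section 7.5 adds a study-level halt: "The study as a whole will be halted if 2/5 patients develop grade 3-4 infusion reactions".

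**The concern.** The same event gets opposite scores from two rules in one section, and no sentence ranks them. The event is foreseeable. Section 4.2 makes toxicity during and within 24 hours of infusion the primary safety endpoint, and section 6.2.3 has steroids and norepinephrine on hand in the infusion unit for emergency use.

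The score governs tier expansion, the MTD count and the dosing of the next patient. In an open-label trial, the choice between the rules would be made after the event is known. Sections 7.4 and 7.5 also stop the infusion and describe no restart. Under the definition, a tier could therefore read 0/3 although one patient had a grade 3-4 reaction and did not receive the full tier dose.

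**Working it through.** The protocol states no operating characteristic for the DLT rule, so there is no planned figure to reproduce. The first check is textual; the second shows how often the ambiguity could arise.

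**Scoring by case (grade 3-4 reaction)**

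| Event | 7.4 paragraph 2 and 7.5 | DLT definition |
|---|---|---|
| Begins during infusion, responds to care | DLT | Not a DLT |
| Begins during infusion, does not respond | DLT | Exception does not apply |
| Begins after infusion, responds to care | Silent | Not a DLT |

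Only the first row is in conflict.

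**Effect of the score on the count**

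- One such event in a tier of three, no other DLT: 0/3 if not scored (eligible to escalate, subject to the other conditions) or 1/3 if scored (add at least three patients).
- One such event in a level of six with one other DLT: 1/6 (can be the MTD) or 2/6 (cannot).
- Two such events in a tier of three would normally trigger the 2/5 halt in section 7.5 under either scoring. The practical conflict is therefore the single event.

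**How often exactly one event occurs in a tier**

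Input: p, the probability per patient of a grade 3-4 reaction that begins during infusion and responds to care. The protocol gives no value for this product. The toxicity table in section 1.4 shows one grade 3 event (hypertension) among 23 patients given third-party cord-blood Tregs. Onset and response to care are not stated, so 1/23 is illustrative only. A range of 2% to 10% is assumed alongside it.

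Per tier of three: 3p(1−p)². At least one of four tiers: 1 − [1 − 3p(1−p)²]⁴.

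| p | Per tier | At least one of four tiers |
|---|---|---|
| 2% | 3 × 0.02 × 0.98² = 5.8% | 21% |
| 1/23 | 3 × (1/23) × (22/23)² = 11.9% | 40% |
| 10% | 3 × 0.10 × 0.90² = 24.3% | 67% |

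The exact 95% interval for 1/23 is 0.1% to 21.9%. It gives 0.3% to 40% per tier and 1% to 87% over four tiers, so the data cited cannot narrow this.

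**Effect on clearing tiers 1 to 3**

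Assume no other DLTs, the same p in every tier, and only the DLT table acting. If the event is scored, a tier is cleared with probability (1−p)³ + 3p(1−p)⁵. At 1/23 this is 0.8752 + 0.1044 = 0.9796, and 0.9796³ = 0.940. If it is not scored, the probability is 1.

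That contrast leaves out the study halt. Simulating with a halt at any 2 of 5 consecutive patients (one reading of the 2/5 rule) gives:

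| p | Scored | Not scored |
|---|---|---|
| 1/23 | 94% | 96% |
| 10% | 74% | 82% |

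Once the halt is included, the effect on reaching tier 4 is modest. The larger effect is on tier expansion and the MTD count.

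**The case against.** The strongest reply is that a workable reading exists. The rule on toxicity during the infusion is specific, mandatory and stated twice, whereas the definition is general and speaks of the weeks after administration. Reading the specific over the general makes infusion-time events DLTs and leaves the exception for later reactions. That reading is sensible, but the text does not compel it. The exception names infusion reactions without limiting their onset, and each rule is specific in its own way: one by timing, the other by type of reaction and response.

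Second, other safeguards act on the same event. Taken literally, section 4.1 bars escalation after any infusion-related side effect. The condition under the schedule of events bars it if the event is serious. Section 7.4 requires review before the next patient and the next cohort. This stands as a limit on size: the percentages above are frequencies of the ambiguous event, not of a different escalation decision. In tier 4, moreover, there is no next level; over the three tiers that can escalate, the figure at 1/23 is 1 − (1 − 0.1193)³ = 32%. But these safeguards do not say whether three patients are added, which matters in tier 4 too, or how the event enters the MTD count. A grade 3 reaction that resolves also need not be serious under section 9.1.

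Third, the immediate protection of the patient is not in dispute, because the infusion stops whichever way the event is scored. That is correct. The conflict concerns the count, not bedside management.

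**Conclusion.** The concern holds. The protocol gives two incompatible scores for a grade 3-4 reaction that begins during the infusion and responds to care, and no order of precedence. The scope is narrow: it is in practice a single event, since two in a tier would normally halt the study anyway. The consequence is real for tier expansion, the within-tier gate and the MTD.

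The frequency depends on an unknown rate: 5.8% to 24.3% per tier over an assumed 2% to 10%, and 11.9% at the illustrative 1/23. These figures assume independent patients, a constant rate and three patients per tier; the four-tier figures further assume that all four tiers open. The point should be fixed before dosing decisions rest on the count, but it does not undermine the design as a whole.

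**What to change.** State one rule in the DLT definition and use the same wording in the second paragraph of 7.4 and in 7.5. Suggested sentence for the definition: *The supportive-care exceptions do not apply to grade 3-4 toxicity that begins during the infusion or causes it to be stopped; such an event is always a DLT.* This adopts the conservative rule the protocol already states twice. If the sponsor prefers the exception, the two sentences on toxicity during the infusion must carry it as well. The 2/5 halt can stay as a separate backstop.

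The drafting cost is one sentence and two matching edits. Under the conservative rule a tier is sometimes expanded for a reversible reaction. At 1/23 that is 3 × 0.119 = 0.36 extra patients per tier, or 4 × 3 × 0.1193 = 1.43 over four tiers, ignoring early stops.
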